##### LBPP incidence, frequency, and intensity

Lumbar and pelvic pain presence and intensity will be evaluated using recommended clinical tests [6, 31] and a 100-mm visual analog scale (VAS) [39]. The construct validity of the visual analog scale has been shown to be significantly and positively correlated with other self-reported measures of pain intensity (i.e., 101-point numerical rating scale, 11-point box scale, 6-point behavioral rating scale, 4-point verbal rating scale, and 5-point verbal rating scale) [40, 41]. Furthermore, participants will receive weekly text messages to collect information about the incidence (first episode during pregnancy), frequency (number of days), and intensity of LBPP. The minimal clinically important difference (MCID) for this outcome will be set according to Hagg et al. (2003) who defined the difference in the score change between patients assessing themselves as “better” and those assessing themselves as “unchanged”. The MCID for this outcome will be 18–19 mm on a 100-mm VAS scale [42].

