### Eligibility criteria

Pregnant women aged 18–40 years old, carrying one fetus and being ≤ 20 weeks pregnant (based on the ultrasound performed in the first trimester of pregnancy) and presenting with a history of LBPP (currently in pain or not) will be eligible to participate in the study. Women undergoing their first LBPP episode (of at least 2 weeks duration) will also be included. The inclusion criteria are based on the potential full-scale trial objective to reduce LBPP recurrences or limit its intensity in pregnant women with a history of LBPP. To confirm the presence and intensity of LBPP and women’s eligibility for the trial, a medical history and recommended clinical tests [6, 31] will be conducted at the pre-intervention visit (baseline) by a member of the research team. Women presenting any of the following conditions will be excluded from the study: inflammatory rheumatic disease, infectious disease, neuromuscular disease, vascular disease, connective tissue disease, severe disabling pain, and neurologic signs and symptoms. Women presenting contraindications to exercise (according to the 2019 Canadian guideline for physical activity throughout pregnancy [21]) will also be excluded from the study. Women unable to understand or speak French as well as those unwilling to be randomized will also be excluded.

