#### Intervention group

Pregnant women in the intervention group will participate in three 40-min exercise sessions per week from ≤ 20 weeks of gestation until 34–36 weeks of gestation: one supervised group session via the Zoom platform (once a month, this session will take place at the *Université du Québec à Trois-Rivières*) and two unsupervised sessions at home.

All sessions will include a 5-min warm-up period followed by specific exercises of moderate-intensity aimed at strengthening muscles of the lumbo-pelvic-hip core complex in order to improve stabilization and alignment of the spine and pelvis (transversus abdominis, internal obliques, multifidus, pelvic floor, thigh, and hip muscles) [36, 37]. The sessions will end with gentle stretching. No specific equipment will be needed to complete the home exercise component of the program. The intervention will be adapted to the stage of pregnancy and related discomfort to ensure a safe, individualized, and yet motivating training experience for each participant. Women will receive a weekly text message with an individually tailored home-exercise program to be completed before the next group session. The text message will contain a link giving access not only to the weekly exercise program, but also to a web-based electronic diary to help participants document their participation in the home exercise sessions (compliance and adverse events), incidence (a painful episode), frequency, and intensity of daily LBPP, as well as any treatment received to prevent and treat LBPP. Participants of this group will also access the same standard prenatal care recommendations as the control group, which includes basic information about what to do when suffering from LBPP, which is provided in the practical guide“ *From Tiny Tot to Toddler”* [35]*.*

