#### Secondary outcome measures

The potential effectiveness of the intervention will be assessed using the following clinical outcomes and assessment tools. All secondary outcome measures (i.e., LBPP incidence, frequency and intensity, functional disability and physical activity levels) will be obtained during the pre-intervention (≤ 20 weeks of gestation) and post-intervention (34–36 weeks of gestation) visit at the university laboratory. Fear avoidance behaviors the level of anxiety, and depression will also be assessed pre- and post-intervention, as they are considered potential prognostic factors (and confounding variables) of LBPP [38].

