### Statistical analysis

Demographic data will be presented using means and standard deviations. For primary outcome measures (recruitment, retention, adherence rate, safety, and acceptability), means, standard deviations and/or percentage will be presented. For secondary outcomes measures, descriptive statistics will be used to describe within-group changes from baseline visit to post-intervention visit (34-36 weeks of pregnancy). Differences between group in mean change with confidence intervals and effect sizes (Cohen’s *d*) will be reported for each measure.

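### As specified, LBPP incidence does not estimate recurrence: it has two definitions, takes in women already in pain, and is summarised as a mean change

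*Protocol article*

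**What the plan says.** **Definition.** In the section on LBPP incidence, frequency and intensity, weekly text messages to participants collect "information about the incidence (first episode during pregnancy), frequency (number of days), and intensity of LBPP". In the Intervention group section, a web diary reached through a link in the weekly message records "incidence (a painful episode), frequency, and intensity of daily LBPP". That diary is described for the intervention group only.

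**Population.** Under Eligibility criteria, a woman "presenting with a history of LBPP (currently in pain or not) will be eligible to participate in the study". The same section adds: "Women undergoing their first LBPP episode (of at least 2 weeks duration) will also be included".

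**Timing.** Secondary outcome measures states: "All secondary outcome measures (i.e., LBPP incidence, frequency and intensity, functional disability and physical activity levels) will be obtained during the pre-intervention" and post-intervention visits. Table 1 also marks LBPP incidence, frequency and intensity as collected throughout the study.

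**Analysis.** For secondary outcomes, "descriptive statistics will be used to describe within-group changes from baseline visit to post-intervention visit". The next sentence adds "Differences between group in mean change with confidence intervals and effect sizes" (Cohen's d) for each measure, with no exception for incidence.

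**Aim.** The objective and second hypothesis in the Background speak of fewer recurrences or lower intensity. The article does not define recurrence as an outcome.

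**The concern.** A first episode of the pregnancy can happen at most once; a painful episode can happen repeatedly. The two wordings give different counts from the same reports. Under the first, a woman in pain at the baseline visit has already had the event, so nothing that happens after allocation can change her status. A yes/no outcome also has no useful change score, and Cohen's d does not suit it.

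At stake is the reading of one secondary outcome. The figure reported as incidence could be taken as evidence on prevention of recurrence when it partly reflects recovery, or could look small because part of the sample could not have the event. Anyone using it to plan the full trial would carry that error forward.

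**Working it through.** **The plan's own figures.** 20 + 20 = 40 women. No recurrence rate or share in pain at entry is given, so there is no planned incidence figure to reproduce. The values below are assumptions, chosen to show direction and size.

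**Step 1: who can have the event.**
- First episode of the pregnancy: a woman in pain at baseline cannot have it after allocation. Nor can a woman who is pain-free at the visit but had an episode earlier in this pregnancy.
- Any painful episode: a woman in pain at baseline could have a further one once the current one resolves.

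So the two definitions differ in who is at risk as well as in what is counted.

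**Step 2: apply the mean-change rule.** Let q be the share in pain at baseline, assumed 30%, 50% or 70%. Assume onset among pain-free women is 60% in controls, and 30% under exercise if it prevents recurrence. Assume resolution among women in pain is 20% in controls, and 50% under exercise if it speeds recovery.

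*Coding A, pain present or absent at each visit:* mean change = (1 − q) × onset − q × resolution. At q = 50%:
- control: 0.5 × 0.6 − 0.5 × 0.2 = 0.20
- exercise prevents onset only: 0.5 × 0.3 − 0.5 × 0.2 = 0.05, difference −0.15
- exercise speeds resolution only: 0.5 × 0.6 − 0.5 × 0.5 = 0.05, difference −0.15

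Two different effects give the same result.

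*Coding B, ever or never had an episode in this pregnancy* (women counted as never at baseline are taken to be all those pain-free): women in pain are events at both visits and contribute zero change. Post-visit proportion = q + (1 − q) × onset. The difference is (0.6 − 0.3) × (1 − q) = 0.3 × (1 − q), whether taken on proportions or on change.

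**Step 3: precision after the fix.** Women at risk per arm = 20 × (1 − q). The Wald 95% half-width for 60% vs 30% is 1.96 × √[(0.6 × 0.4 + 0.3 × 0.7)/n] = 1.96 × √(0.45/n).

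| q | A: onset effect only | A: resolution effect only | B: control vs exercise | At risk per arm | Half-width, points |
|---|---|---|---|---|---|
| 30% | −0.21 | −0.09 | 72% vs 51% = 21 points | 14 | 35 |
| 50% | −0.15 | −0.15 | 80% vs 65% = 15 points | 10 | 42 |
| 70% | −0.09 | −0.21 | 88% vs 79% = 9 points | 6 | 54 |

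With all 20 per arm at risk the half-width would be 29 points. At the 80% retention named in the progression criteria, the numbers at risk fall to about 11, 8 and 5 per arm.

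**The case against.** **It is a feasibility trial.** Effectiveness is secondary and only potential, no progression criterion uses incidence, and the Sample size section plans the next trial from differences in LBPP and disability score without naming an incidence rate. This stands and limits the weight of the point. Forty women would not settle recurrence even with a clean definition, and the article does not claim they would.

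**The mixed population is deliberate.** The hypothesis covers recurrence or intensity, and baseline pain intensity is a minimization criterion. This also stands: admitting both kinds of women is no error. But minimization balances the arms; it does not change who can have the event or what the summary measures.

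**Detail belongs in the analysis plan.** Subgroup reporting may well be there. The two definitions and the rule covering every measure, however, are written in this article.

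**Stronger readings a reader might infer, which the documents do not support:**
- *That the recurrence question cannot be answered.* Pain presence is assessed at baseline and participants report weekly, so new episodes in women pain-free at baseline can be derived. Under coding B the effect is diluted, not lost.
- *That pain-day counts are distorted by unequal follow-up.* The article does not say raw totals will be compared, and randomisation balances entry date in expectation.
- *That VAS change fails for women starting at 0 mm.* The between-arm contrast is still valid; prevention appears as a smaller rise.
- *That ascertainment is unequal between arms.* The diary is described for one arm only, but the weekly text messages are described for participants generally. Unequal ascertainment is a risk to close off, not an established fault.
- *That women in a first-ever episode need their own rule.* They are in pain at entry and so fall outside an at-risk set of pain-free women.

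**Conclusion.** The point holds in a limited form. As specified, the incidence outcome and its planned summary do not estimate recurrence. The conflict between definitions and the unsuitable summary rest on the text alone. The size rests on assumptions: with 30% to 70% of women in pain at entry, a true 30-point difference would show as 21 to 9 points under ever/never coding. Under present/absent coding, onset and resolution effects cannot be told apart, and at 50% in pain they coincide at −0.15 for the assumed rates. The direction does not depend on the rates: whenever some women are in pain at entry, coding B dilutes the risk difference by the factor (1 − q), and coding A lets resolution contribute. The feasibility outcomes, the progression criteria, VAS intensity and the PGQ are unaffected.

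**What to change.** 1. Use one definition in both sections: a new LBPP episode after allocation among women pain-free at the baseline visit, with pain-free status taken from the assessments already planned there.
2. Ascertain it by the same weekly text messages in both arms. If the diary stays specific to the intervention group, do not use it for this outcome.
3. Report the number at risk and the proportion with an episode per arm, and the risk difference with 95% CI.
4. In Statistical analysis, exempt incidence from the mean-change and Cohen's d rule. Keep that rule for VAS intensity and the PGQ, optionally also shown by baseline pain status.

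The cost is wording and a table row or two, using data already to be collected. The downside is a smaller denominator and a wider interval for incidence: for the assumed 60% vs 30%, a half-width of about 35 to 54 points instead of 29. That is an honest statement of what the trial can say about recurrence.

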##### Functional disability

Functional disability will be measured using the Pelvic Girdle Questionnaire (PGQ) [43]. The PGQ is a 25-item questionnaire scored on a Likert-type scale that includes a 20-item activity subscale and a 5-item symptoms subscale. Items 1–20 and 23–25 scores range from 0 (not at all) to 3 (to large to extent) while items 21 and 22 scores range from 0 (none) to 3 (considerable) [43]. The MCID for this outcome will be 11 points [44].

##### Physical activity levels

Physical activity levels will be measured using the Pregnancy Physical Activity Questionnaire (PPAQ) [45]. The PPAQ is a self-administrated 33-question questionnaire which provides a comprehensive assessment of four domains of physical activity including “Sports and Exercises” (*n* = 9), “Household and Caregiving” (*n* = 16), “Transportation” (*n* =3), and “Occupation” (*n* = 5) [45].

##### Fear avoidance behavior

The fear avoidance behavior will be measured using the Tampa Scale of Kinesiophobia (TSK) [46]. The TSK comprises 17 questions evaluating the fear of movement and physical activities resulting from being afraid to get hurt; it uses a Likert-type scale ranging from “strongly disagree” to “strongly agree” [47].

##### Anxiety

Anxiety levels will be measured using the State-Trait Anxiety Inventory (STAI-Y) [38]. The STAI-Y comprises two distinct scales: situational anxiety and anxiety trait. The situational anxiety is composed of 20 sentences assessing the current emotional state of the individual. The individual indicates the emotion intensity on a Likert-type scale ranging from “not at all” to “a lot” [38]. The anxiety trait is composed of 20 sentences assessing habitual emotional state of an individual. The individual indicates the frequency with which she usually feels the symptoms on a Likert-type scale ranging from “almost never” to “almost always” [38].

##### Depression

Depression levels will be measured using the Beck Depression Inventory (BDI) [48]. The BDI is a 21-item questionnaire evaluating different specific behavioral manifestation of depression on a Likert-type scale reflecting the severity of depression symptoms [48].

#### Additional assessments

Participants will answer several questions during the pre-intervention visit to collect the following information: age, gestational age, pre-pregnancy weight, and educational level. Height and weight will be measured at the pre- and post-intervention visits.

The timeline illustrating the various interventions and outcome assessments is presented in Table 1.

**Table 1 Tab1:** Schedule of laboratory visits, intervention and outcomes measures

	Study period			
Timepoint	Enrolment	Pre-intervention	Throughout the study	Post-intervention
**Enrolment:**				
**Eligibility screen**	X			
**Informed consent**	X			
**Allocation**		X		
**Interventions:**				
***Control group***			X^a^	
***Intervention group***			X^b^	
**Assessments:**				
***Primary outcomes measures***				
***Recruitment rate***		X		
***Retention rate***				X
***Adherence rate***				X^c^
***Safety of the intervention***			X^c^	X^c^
***Acceptability of the intervention***				X
***Secondary outcomes measures***				
***LBPP incidence, frequency and intensity***		X	X	X
***Functional disability***		X		X
***Physical activity levels***		X		X
***Fear avoidance behavior***		X		X
***Anxiety***		X		X
***Depression***		X		X

Pre-intervention visit (≤ 20 weeks of gestation); throughout the study (between pre-intervention and post-intervention visits); post-intervention visit (34–36 weeks of gestation)

^a^Standard prenatal care

^b^Motor control exercise program at UQTR and at home as well as standard prenatal care

^c^Intervention group only

### Statistical analysis

Demographic data will be presented using means and standard deviations. For primary outcome measures (recruitment, retention, adherence rate, safety, and acceptability), means, standard deviations and/or percentage will be presented. For secondary outcomes measures, descriptive statistics will be used to describe within-group changes from baseline visit to post-intervention visit (34-36 weeks of pregnancy). Differences between group in mean change with confidence intervals and effect sizes (Cohen’s *d*) will be reported for each measure.

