### Sample size

Pregnant women will be recruited and randomly allocated to a control (20 participants) or intervention (20 participants) group. A sample size of 40 pregnant women was chosen based on a previous study we conducted and in which we were able to recruit 40 pregnant women in twelve months [32] and considering that over 4600 women gave birth at the local health services in 2016–2017 (including 1800 at the *CIUSSS-MCQ*) [33]. Furthermore, one of the study goals is to obtain an estimate of variance for the primary outcomes of a full-scale study. A minimally clinical important difference between groups has already been established and it is suggested that 10 to 20 participants per group is sufficient to inform feasibility and to plan for a larger study [34]. Between group differences in LBPP and disability score after the intervention will be used to estimate adequate sample size for future research planning.

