### Progression criteria

The following criteria must be met in order to consider progression to a main RCT:Recruitment criteria: recruitment rate of 40 eligible women over a 12-month period.Retention criteria: retention rate of ≥ 80% of recruited women.Adherence criteria: adherence rate of ≥ 75% to the supervised and unsupervised exercise sessions.Safety criteria: less than 25% of women experiencing acute LBPP flare-ups interfering with daily activities.

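### The primary feasibility rates that gate a main trial are planned without intervals, while the secondary outcomes get them; a bare pass on 20 or 40 women leaves failing rates well within range

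*Protocol article*

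**What the plan says.** In the protocol article, Statistical analysis fixes the summary of the primary outcomes: "For primary outcome measures (recruitment, retention, adherence rate, safety, and acceptability), means, standard deviations and/or percentage will be presented". For the secondary outcomes the same section goes further and plans "Differences between group in mean change with confidence intervals and effect sizes".

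Progression criteria opens with "The following criteria must be met in order to consider progression to a main RCT". The criteria are:
- recruitment: "recruitment rate of 40 eligible women over a 12-month period"
- retention: "retention rate of ≥ 80% of recruited women"
- adherence: "adherence rate of ≥ 75% to the supervised and unsupervised exercise sessions"
- safety: "Safety criteria: less than 25% of women experiencing acute LBPP flare-ups interfering with daily activities"

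Neither section mentions an interval, an intermediate zone or any other way of handling uncertainty around these cut-offs. Acceptability is a primary outcome but has no cut-off.

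Sample size gives 20 women per group. Under Primary outcome measures, adverse-event information is collected in the intervention group, and adherence and retention are evaluated there too. Table 1 marks adherence and safety as intervention group only but does not mark retention, and the retention criterion refers to recruited women, who number 40.

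**The concern.** Feasibility is the primary objective, and the feasibility rates are what a decision on a main trial must pass through. Yet the article plans a statement of uncertainty only for the secondary effectiveness results. On 20 or 40 women, a percentage that lands just inside a cut-off says little about which side the true rate lies on.

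At stake is how a pass will be read. If an observed 20% flare-up rate or 80% retention is set against its threshold with nothing beside it, planners of the main trial may take safety or retention as established when the data still allow a rate that would fail the same criterion. The reverse also occurs: a truly acceptable rate can miss the cut-off by chance.

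**Working it through.** **The plan's own figure.** The sample size is 20 + 20 = 40. It rests on past recruitment, a rule of thumb for group size and the aim of estimating variance. No precision target is stated, so there is no formula to reproduce.

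**Inputs.** Thresholds are from Progression criteria and group sizes from Sample size. For safety n = 20 (intervention group). For retention n = 40 (recruited women, Progression criteria) or n = 20 (intervention group, Primary outcome measures). The 95% two-sided level is an assumption, because the article names no level for these outcomes.

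**Smallest passing results.**
- Safety: below 0.25 × 20 = 5, so at most 4/20 = 20%.
- Retention: 0.80 × 40 = 32, so at least 32/40; or 0.80 × 20 = 16, so at least 16/20.

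**Exact (Clopper-Pearson) interval for x of n.** The lower limit is the 0.025 quantile of Beta(x, n − x + 1); the upper limit is the 0.975 quantile of Beta(x + 1, n − x).

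| Result | Estimate | Exact 95% interval | Wilson check |
|---|---|---|---|
| Safety 4/20 | 20% | 5.7% to 43.7% | 8.1% to 41.6% |
| Retention 32/40 | 80% | 64.4% to 90.9% | 65.2% to 89.5% |
| Retention 16/20 | 80% | 56.3% to 94.3% | 58.4% to 91.9% |

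**Chance that each criterion is met, taken alone, at an assumed true rate p (binomial).**
- Safety, P(X ≤ 4 | n = 20): 63.0% at p = 20%, 41.5% at 25%, 23.8% at 30%, 11.8% at 35%.
- Retention, P(X ≥ 32 | n = 40): 11.1% at p = 70%, 30.0% at 75%, 86.5% at 85%. At a true 85% it therefore fails 100 − 86.5 = 13.5% of the time.
- Retention, P(X ≥ 16 | n = 20): 23.8% at p = 70%, 41.5% at 75%, 83.0% at 85%.

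**Adherence.** If it is scored as a mean percentage per woman, the interval is mean ± t(0.975, 19) × SD/√20. The article gives no SD, so a range is assumed. At a mean of 75%, an SD of 15 points gives 68.0% to 82.0%, 25 points gives 63.3% to 86.7%, and 35 points gives 58.6% to 91.4%.

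**What it takes for the interval to clear the threshold.** Safety needs at most 1/20. Retention needs at least 38/40, or 20/20 with the smaller denominator. Most passing results would therefore leave a failing rate inside the interval.

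**Recruitment.** The criterion and the planned sample are both 40, so the count is capped at its target. An interval for an uncapped count does not fit it, and none is used here.

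**The case against.** The strongest reply is that this is a short journal article, that saying what will be presented does not rule out intervals, and that the interval method for a descriptive rate belongs in the analysis plan. This would carry weight if the article were silent. It is not: it states the summary for the primary outcomes and, in the same section, names intervals for the secondary ones only. The point is an improvement to a stated method.

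A second reply is that little information is lost. Standard deviations are listed, so a reader could build an interval for mean adherence, and a percentage with a known denominator yields an exact interval. That is true, but it leaves the reported result and the progression judgement without one, and for retention the denominator itself is unsettled.

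Several stronger readings are tempting, and the document does not support them:
- A reader might infer that these rates alone decide progression. The wording is "The following criteria must be met in order to consider progression to a main RCT", which makes them necessary conditions for considering a main trial, not an automatic go.
- A reader might infer that the article prescribes a comparison of point values. No sentence says so; it is the natural reading of single cut-offs with no uncertainty rule.
- A reader might take the pass probabilities above as the chance of overall success. The criteria apply jointly, and each figure is for one criterion alone.
- A reader might conclude that the trial is too small, or that the claim "it is suggested that 10 to 20 participants per group is sufficient to inform feasibility and to plan for a larger study" is wrong. That claim rests on a cited source that cannot be checked here, and low precision is inherent in a feasibility trial.

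**Conclusion.** The point holds as a cheap improvement, not as a flaw in the design. The article attaches intervals to the secondary results and not to the primary ones, although the primary ones carry the conditions for a main trial.

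A just-passing safety result of 4/20 is compatible with a true flare-up rate from 6% to 44%, and the criterion is met 24% of the time at a true 30%. A just-passing retention of 80% is compatible with 64% to 91% on 40 women, or 56% to 94% on 20. It is met 30% or 41% of the time, respectively, at a true 75%.

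These figures assume the full 20 + 20 women are enrolled, all 20 intervention women count in the safety denominator, women are independent, and a 95% level applies. The adherence intervals also depend on an assumed SD and on per-woman scoring.

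**What to change.** 1. **Statistical analysis:** report retention and safety with exact (Clopper-Pearson) 95% intervals, and mean per-woman adherence with a t or bootstrap 95% interval. Do not add a Poisson interval for recruitment.
2. **Progression criteria:** keep the thresholds. Add that the progression judgement is made and reported with each estimate beside its interval, so that a met criterion is not described as excluding a failing rate when the interval crosses the threshold. A compulsory label for such results is not advised: with clearance needing at most 1/20 or at least 38/40, it would attach to nearly every pass and separate little.
3. **Primary outcome measures and Progression criteria:** reconcile the retention denominator (intervention group or all recruited women) and use the same one in both.

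The cost is a few lines of text and trivial computation, with no extra participants or data. The downside is a feasibility conclusion that looks less definite.

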The recently published *2019 Canadian guideline for physical activity throughout pregnancy* [20] clearly highlights that, not only is exercise safe for both the mother and the growing fetus, but that it also improves key pregnancy outcomes such as decreased risk of gestational hypertension and diabetes [22], excessive gestational weight gain [23] and depression [28]. The guideline summarizes the best available evidence and provides consensus-based recommendations on physical activity during pregnancy. It suggests that women without any medical restriction should accumulate at least 150 min of a variety of moderate-intensity physical activity each week to achieve clinically meaningful reduction in pregnancy complications, such as gestational diabetes mellitus, gestational hypertensive disorders, and prenatal depression [21]. Nonetheless, the guideline does not provide any specific recommendation for the prevention and treatment of LBPP during pregnancy, mainly due to the lack of evidence regarding the effect of prenatal exercise on the occurrence of pregnancy-related LBPP and the poor quality of evidence (i.e., “very low”) and heterogeneity of the data regarding its effect on LBPP intensity [22]. Considering that a history of LBPP is one of the strongest predictors of LBPP during pregnancy [15] and that it is a debilitating condition associated with significant personal, social, and economic burden [17, 18, 29], exercise may offer a safe and cost-effective self-management strategy option to decrease the recurrences and symptom intensity of LBPP for expecting mothers with a history of LBPP. However, more robust research is needed to identify suitable or effective exercise modalities to optimize self-management of LBPP in these women.

The primary objective of the study described in this protocol is to assess the feasibility of implementing a motor control exercise program with pregnant women presenting a history of LBPP in order to reduce LBPP recurrences or limit its intensity. The secondary objective is to assess the potential effectiveness of the program. The first hypothesis is that the motor control exercise program will show high recruitment, adherence rates as well as low attrition among pregnant women with a history of LBPP in the intervention group. The second hypothesis is that the proposed motor control exercise program will reduce LBPP recurrences or limit its intensity.

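### The stated analysis reads lumbopelvic pain only as change between two visits, so it cannot address recurrence and leaves the weekly pain reports without a between-arm comparison

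*Protocol article*

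**What the plan says.** The second hypothesis, at the end of the Background, is that "the proposed motor control exercise program will reduce LBPP recurrences or limit its intensity".

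The Statistical analysis section has one rule for all secondary outcomes: "descriptive statistics will be used to describe within-group changes from baseline visit to post-intervention visit (34-36 weeks of pregnancy". The between-arm comparison follows from it: "Differences between group in mean change with confidence intervals and effect sizes", reported for each measure. The Secondary outcome measures section agrees with that rule. It lists LBPP incidence, frequency and intensity among the outcomes that "will be obtained during the pre-intervention (≤ 20 weeks of gestation) and post-intervention (34–36 weeks of gestation) visit at the university laboratory".

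The section on LBPP incidence, frequency, and intensity adds a second stream of data: "participants will receive weekly text messages to collect information about the incidence (first episode during pregnancy), frequency (number of days), and intensity of LBPP". Table 1 agrees with this stream. Its row "LBPP incidence, frequency and intensity" is marked before, during and after the intervention, and the middle column means "throughout the study (between pre-intervention and post-intervention visits". The footnote "Intervention group only" is attached to adherence and safety but not to the LBPP row.

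The Sample size section says that between-group differences in LBPP and disability after the intervention will be used to plan the size of the next trial.

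**The concern.** The protocol collects LBPP in two ways but states an analysis for only one. The one it analyses, a reading at each of two visits at least 14 weeks apart, is the one that cannot show whether pain recurred in between. The weekly stream, which could show it, has no stated between-arm use.

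At stake is the secondary objective, potential effectiveness, and the LBPP effect and variance carried into the full trial. If only two-visit change is reported, half of the hypothesis (fewer recurrences) goes unanswered. The intensity estimate is also less precise than the planned data collection allows.

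**Working it through.** **1. Match each LBPP component to the stated rule.** No figure in the plan is in dispute. The sample size of 40 rests on recruitment experience and a 10–20 per group guide, so there is no power calculation to reproduce.

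- *Incidence*, defined in the outcome section as the first episode during pregnancy, is an event. It has no meaningful mean change from baseline and no natural Cohen's d.
- *Frequency*, a number of days, is collected weekly between the visits. A baseline frequency is scheduled in Table 1, so a change can be defined, but two visit values do not add up the pain-days between them.
- *Intensity* fits the rule, but only the two visit values enter it.

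**2. What one visit can miss.** Entry at 20 weeks and a final visit at 34–36 weeks give 14–16 weeks of follow-up; take 15. If a woman has pain in 4 of 15 weeks, a randomly placed visit falls in a pain-free week with probability 1 − 4/15 = 0.73. For 7 of 15 weeks it is 1 − 7/15 = 0.53. The numbers of painful weeks are assumed.

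**3. Precision for intensity.** Assumptions (the documents give no SD or correlation): equal SD at all times, equal correlation ρ between any two readings, r = 14 weekly reports. Variances are in units of SD².

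- Planned two-visit change: 2(1 − ρ)
- Unadjusted weekly mean: (1 + 13ρ)/14
- Single final reading adjusted for baseline: 1 − ρ²
- Weekly mean adjusted for baseline: (1 + 13ρ)/14 − ρ²

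| ρ | Planned change | Unadjusted weekly mean | Adjusted final reading | Adjusted weekly mean |
|---|---|---|---|---|
| 0.3 | 1.40 | 0.35 | 0.91 | 0.26 |
| 0.5 | 1.00 | 0.54 | 0.75 | 0.29 |
| 0.7 | 0.60 | 0.72 | 0.51 | 0.23 |

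The planned change has 5.4, 3.5 and 2.6 times the variance of the adjusted weekly mean. Part of that gain comes from baseline adjustment alone.

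The unadjusted weekly mean is not always better than the plan. Setting 2(1 − ρ) = (1 + 13ρ)/14 gives 28 − 28ρ = 1 + 13ρ, so ρ = 27/41 ≈ 0.66. Above that value it is noisier than the planned change.

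**4. In millimetres.** The half-width of the 95% interval is t × SD × √(2/n) × √variance, with 2n − 2 degrees of freedom. With an assumed SD of 25 mm and ρ = 0.5:

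- 20 per arm: 16.0 mm for the planned change, 8.6 mm for the adjusted weekly mean.
- 16 per arm (80% retention, 0.8 × 20): 18.1 mm and 9.6 mm.

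Over SD 20–30 mm and ρ 0.3–0.7 with 20 per arm, the ranges are 9.9–22.7 mm and 6.2–10.3 mm. The protocol's minimal important difference is 18–19 mm.

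**The case against.** The strongest reply is that these are secondary, descriptive outcomes of a 40-woman feasibility trial, and that a condensed article need not say how every data stream is summarised. The progression criteria use neither the change in pain score nor pain-days. The two-visit change also has a rationale: the 18–19 mm minimal important difference is defined on score change, and the Sample size section speaks of differences after the intervention. An average over pregnancy is a different quantity from pain at the end of the programme, and a visit could ask about past weeks.

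Much of this stands. It limits the importance of the point and is a reason to keep the visit-to-visit change. It does not remove the mismatch. The article does more than stay silent: it assigns one rule to each secondary measure, and that rule does not suit incidence or recurrence. No recall period is stated for the visits.

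Several stronger readings are tempting but are not supported:

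- *A pain-free visit day makes a woman a success.* No responder classification is planned, and the recall period of the pain scale is not given.
- *Pain-day counts favour late entrants and women who do not answer texts.* No cumulative raw count is planned, and randomisation balances entry week in expectation.
- *Frequency has no baseline.* One is scheduled at the pre-intervention visit.
- *Weekly averaging cuts the SD by 41%, 27% or 15%* at ρ = 0.3, 0.5 or 0.7. That compares an unadjusted weekly mean with a single follow-up reading, whereas the plan compares change.
- *Weekly data are certainly collected alike in both arms.* This is inferred from the word participants and from the absent table footnote. The Intervention group section describes the text link and diary, with LBPP items, for that arm only.

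**Conclusion.** The point holds in a limited form. The stated comparison does not address the hypothesis of fewer recurrences, and it leaves without a stated between-arm use weekly data that bear on it directly. This follows from the text and needs no numerical assumption.

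The size of the precision gain does rest on assumptions: equal correlation, common SD, 14 complete reports and adjustment for baseline. Under these the variance of the intensity comparison falls by a factor of 2.6 to 5.4. Autocorrelated weekly scores and unanswered texts would make it smaller. A reader might infer that the two-visit change is the wrong endpoint for the full trial; the documents do not support that, and the choice between end-of-programme pain and average pain remains open. The consequence is confined to the effect and variance estimates for LBPP. Feasibility outcomes and progression criteria are untouched.

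**What to change.** In the Statistical analysis section, add between-arm comparisons of the weekly LBPP data over 20–34 weeks of gestation, the window common to all women:

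1. the proportion of women with a new LBPP episode;
2. pain-days per week with a returned text, adjusted for baseline frequency;
3. mean weekly intensity, adjusted for baseline intensity, which is already a minimisation factor.

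Define an episode once, and say how women already in pain at entry are counted. The outcome section equates incidence with the first episode in pregnancy, while the Intervention group section equates it with a painful episode.

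Keep the visit-to-visit change in pain score alongside. Reconcile the Secondary outcome measures section, which mentions only the two visits, with the outcome section and Table 1. State that the weekly LBPP texts go to both arms in the same form, and report the number returned by arm.

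The cost is wording and a little more analysis; if the texts do go to both arms, no new data are needed. The main risk is that response to the texts may differ between unblinded arms, which is why returns must be shown by arm.
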